#### Statistical analysis

The statistical analysis will be performed by an independent statistician who is not aware of the group allocation. SPSS 21.0 statistical software (IBM SPSS Statistics, New York, USA), will be used for data analysis. The level of significance will be established at α < 0.05 with a two-sided test. Continuous data will be represented as the mean ± standard deviation or median (range), whereas categorical data will be represented by percentage.

All efficacy analyses will be performed using the intent-to-treat (ITT) approach. For the ITT analysis, the population will consist of all patients who have been randomized. Missing data will be imputed using the multiple imputation method. Continuous variables will be compared using a Student’s t-test or Wilcoxon rank-sum test as appropriate. Categorical variables will be compared using Fisher’s exact test or Wilcoxon rank-sum test as appropriate. A preplanned subgroup analysis according to *H. pylori* status will be performed for the primary outcomes.

A sensitivity analysis will be conducted for the primary outcome using per-protocol (PP) population, including only those patients who complete at least 10 sessions and have no major protocol violations (taking other drugs during the trial, not completing the eCRF as required, etc.).

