## Methods

### Study design

This multi-center, randomized, participant-blind, sham-controlled trial will be conducted at five hospitals in China: Dongfang Hospital Affiliated to Beijing University of Chinese Medicine; Dongzhimen Hospital Affiliated to Beijing University of Chinese Medicine; Huguosi Hospital of Chinese Medicine Affiliated to Beijing University of Chinese Medicine; Beijing Hospital of Traditional Chinese Medicine Affiliated to Capital Medical University; and Beijing Friendship Hospital Affiliated to Capital Medical University. The study protocol has been approved by ethics committees at all participating hospitals, will follow the Declaration of Helsinki, and will be reported based on SPIRIT guidelines (Additional file 1) [24]. This trial has been registered with ISRCTN at Current Controlled Trials (ISRCTN12511434). A flow diagram of the trial is shown in Fig. 1.

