### Outcomes

#### Primary outcomes

The two primary outcomes are the response rate based on overall treatment effect (OTE) and the elimination rate of all three cardinal symptoms: postprandial fullness; upper abdominal bloating; and early satiation (no symptoms) at the end of treatment (four weeks after randomization) [26].

When assessing OTE, outcome assessors will evaluate patients using a 7-point Likert scale. The question is “How were your gastric symptoms during the past week in comparison with the baseline period?”, which closely resembles the way physicians evaluate treatment benefit in clinical practice. The answers will include “extremely improved,” “improved,” “slightly improved,” “not changed,” “slightly aggravated,” “aggravated,” and “extremely aggravated” [26]. Patients who answer “extremely improved” or “improved” will be considered as responders. Although there is no universally accepted primary outcome established for therapeutic trials in FD, OTE is a frequently used outcome [27], which has been used as the primary outcome in several trials [28–30].

The elimination rate of three cardinal symptoms was added as another primary outcome. Because the U.S. Food and Drug Administration has argued against the use of OTE as a single primary outcome for its recall bias. After trial commencement, the Data and Safety Monitoring Board (DSMB) suggested that we could use combined primary outcomes for our study. Similarly, the pattern of two primary outcomes was adopted in a study evaluating acotiamide in FD [26]. The elimination rate is based on the severity of dyspepsia symptoms [31] and is defined as the proportion of patients whose scores of postprandial fullness, upper abdominal bloating, and early satiation all decline to 0 [26].

Acupuncture will be considered as an effective therapy, only if both primary outcomes achieve significant difference to avoid type I error accumulation. All protocol amendments are described in detail in Additional file 2.

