### Statistical methods

#### Sample size

Since acupuncture is a complex intervention, it is different from drugs. The efficacy of acupuncture will be altered, if the acupoints in the study are changed. For this reason, literature data speculation is not adopted in this trial. Based on previous clinical experience, the proportions of acupuncture and sham acupuncture responders for OTE are expected to be 55% and 35%, respectively. For elimination of all the three symptoms, the proportions are expected to be 26% and 10%, respectively. A two-sided significance level is 0.05. A sample size of 224 (112 patients in each group) was estimated to have at least 80% power to detect significant differences. The power was calculated as the product of the power of each endpoint: 82.5% and 84.3%. To compensate for a 20% attrition rate, the sample size expands to 140 patients in each group.

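### Multiple imputation is paired with Fisher's exact test, which gives nothing Rubin's rules can pool, so the text does not fix the single p-value each co-primary needs

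*Protocol article*

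**What the plan says.** The Statistical analysis section fixes three things for the efficacy analyses.

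- Population: "For the ITT analysis, the population will consist of all patients who have been randomized".
- Missing data: "Missing data will be imputed using the multiple imputation method".
- Test: "Categorical variables will be compared using Fisher’s exact test or Wilcoxon rank-sum test as appropriate".

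Both primary outcomes are yes/no. OTE response means one of the two best answers on the 7-point scale. Elimination means that all three cardinal symptom scores reach 0. Fisher's exact test is therefore the natural reading for both.

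The Primary outcomes section sets the decision rule: "Acupuncture will be considered as an effective therapy, only if both primary outcomes achieve significant difference to avoid type I error accumulation". The Sample size section adds: "A two-sided significance level is 0.05". The article names no risk difference, odds ratio or model for the primary comparison.

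**The concern.** Multiple imputation produces several completed data sets. Rubin's rules turn them into one inference by averaging an estimate and adding the variance between imputations to the variance within them. Fisher's test supplies neither an estimate nor a variance, only one conditional p-value per data set. The Wilcoxon alternative, as named, also ends in a p-value.

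An analyst who follows the text literally must therefore add a rule for combining p-values. One who pools an effect estimate replaces the named test. The two routes do not have the same error rate. Success depends on two p-values each falling below 0.05, and the plan allows for 20% attrition, so the choice could decide a borderline result.

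**Working it through.** **Inputs from the protocol article.** Sample size section: OTE 55% vs 35%; elimination 26% vs 10%; 112 per arm before attrition; stated powers 82.5% and 84.3%; 20% attrition; 140 per arm. Two-sided 0.05.

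**Assumptions.** 20 imputations; values missing at random; imputation from the arm proportion alone; missing rates of 5% and 10% as alternatives to the planned 20%. Null rates of 10% and 35% are the planned sham rates, and 45% is the OTE average, (55 + 35)/2.

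**Step 1: the plan's own figures.** Continuity-corrected two-proportion test with n = 112:

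power = Φ((δ − 1/n − 1.96·SE0)/SE1), where SE0 = √(2p̄(1−p̄)/n) and SE1 = √((p1(1−p1) + p2(1−p2))/n).

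- OTE: δ = 0.20, SE0 = √(0.495/112) = 0.0665, SE1 = √(0.475/112) = 0.0651. (0.20 − 0.0089 − 0.1303)/0.0651 = 0.93, so power is 82.5% (stated 82.5%).
- Elimination: δ = 0.16, SE0 = √(0.2952/112) = 0.0513, SE1 = √(0.2824/112) = 0.0502. (0.16 − 0.0089 − 0.1006)/0.0502 = 1.00, so power is 84.2% (stated 84.3%).

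Exact enumeration of Fisher's test gives 82.8% and 85.6%. The stated powers thus already correspond to a test about as conservative as Fisher's. Attrition: 112/0.80 = 140, so up to 28 per arm may be missing.

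**Step 2: what can be pooled.** For a risk difference D with variance V in each of m data sets:

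- W = mean of V; B = variance of D between imputations; T = W + (1 + 1/m)B.
- Refer mean(D)/√T to a t distribution with (m − 1)(1 + W/((1 + 1/m)B))² degrees of freedom.

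Fisher's test provides no D and no V, so there is nothing to enter.

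**Step 3: how much the combining rule matters.** Each simulated trial has 140 per arm. With k observed and x responders in an arm, draw q from Beta(x + 0.5, k − x + 0.5), fill in the missing values from Binomial(140 − k, q), and repeat 20 times. Each scenario has 40,000 trials, so the standard error near 5% is √(0.05 × 0.95/40,000) = 0.1 percentage point.

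Null rejection per endpoint, over null rates 10–45%:

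| Missing | Median Fisher p | Mean Fisher p |
|---|---|---|
| 5% | 3.6–4.5% | 3.2–3.9% |
| 10% | 4.1–5.0% | 3.4–3.9% |
| 20% | 5.6–6.7% | 3.6–4.3% |

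The Rubin-pooled risk difference at 20% missing rejects in 5.0–5.4%. I repeated the simulation for this write-up. It agreed within simulation error; the largest median-p value at 10% missing was 5.1%.

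The pattern has a simple cause. The median p ignores the variance between imputations. Fisher's conservatism hides this when little is missing but not at 20%.

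**Step 4: how often the verdict changes.** In 1,000 trials per scenario at 20% missing under the planned effects, the 20 Fisher p-values lay on both sides of 0.05 in 35% (OTE) and 31% (elimination) of trials. Four defensible rules (median p, mean p, normal-score pooling of p-values, Rubin-pooled risk difference) disagreed on significance in about 5% of trials under the planned effects and 2.7% under the null. With 5% missing they disagreed in 1.4–2.9%.

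**The case against.** The strongest reply is that the combining rule is a detail a condensed article properly leaves to the analysis plan, which is not shown. That stands for the number of imputations, the imputation model and the rule itself. It does not remove the point, which concerns two stated choices that do not fit together. An analysis plan that keeps both must add a p-value rule, and one that pools an estimate departs from the named test.

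The reply is also right that 20% is an attrition allowance, not a forecast. Assessors will still try to follow patients who discontinue, and weekly symptom scores could sharpen the imputations. Both would shrink the differences above. The rates are also per endpoint. Because both endpoints must be significant, they are an upper limit on the trial-level false-positive rate.

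A reader might infer four stronger claims that the documents do not support.

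- **That the p-values are undefined.** Recognised ways of combining p-values across imputations exist. The text merely does not choose one.
- **That type I error is badly inflated.** Rates of 8–9% arise only if a single completed data set is analysed. That is single imputation, which the plan does not propose.
- **That Fisher's test costs power the trial did not budget for.** Step 1 shows that the stated powers match a Fisher-type test. The joint power implied by the Sample size section is a separate matter and adds no weight here.
- **That leaving out centre is an error.** The trial "will be conducted at five hospitals in China", but the Randomization and allocation concealment section states no stratification by centre, and an unadjusted comparison is valid under 1:1 randomization.

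**Conclusion.** The point holds as a mismatch between two stated methods: the named test yields nothing that the standard pooling rules for the named imputation method can use. Its size is modest. At the full 20% attrition, the per-endpoint false-positive rate runs from about 3.6% to 6.7% across the two simple Fisher-based rules, against 5.0–5.4% for a pooled risk difference. At 10% missing or less, neither Fisher-based rule exceeds 5% by more than simulation error. Among defensible rules, about 1–5% of trials would change verdict.

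These figures assume data missing at random, 20 imputations and no predictors beyond arm. They would be smaller with informative predictors or less missing data. The point is still worth correcting, because the change needs no new data and removes a choice that could otherwise be made after the results are seen.

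**What to change.** For each co-primary, replace Fisher's test as the primary analysis with a poolable treatment effect.

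1. Impute the OTE category and the three cardinal symptom scores, separately by arm, using the weekly symptom scores already collected. Then derive the two binary endpoints.
2. In each imputed data set, fit a binomial or logistic model with arm and the baseline cardinal-symptom score. Centre is optional.
3. State in advance whether the effect is a risk difference or a log odds ratio. Take it with its standard error, pool by Rubin's rules, test at two-sided 0.05 and report a 95% CI.
4. Keep Fisher's exact test for complete data, such as adverse-event tables.

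The baseline score is an improvement in precision that comes almost free, not the correction of an error. The cost is a change of wording in the protocol or analysis plan and slightly more programming. The one real drawback concerns a sparse endpoint. At the planned 10% sham elimination rate only about 14 of 140 patients have the event, and inference would rest on large-sample theory instead of an exact test. In the simulations the pooled risk difference kept its null rejection near 5% at that rate.

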### Randomization and allocation concealment

All eligible patients will be randomly assigned to the acupuncture group or sham acupuncture group in a 1:1 ratio with a central web-based randomization (Beijing Guide Technology Co., Ltd.). The blocked randomization sequence will be computer-generated with the SAS 9.3 software by a professional statistician, who is not involved in the implementation and statistical analysis of the trial. The clinical research coordinator will be responsible for enrolling patients, obtaining informed consent and requesting randomization.

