### Masking

Due to the nature of acupuncture, masking of acupuncturists is quite difficult to achieve. Patients, outcome assessors, and statisticians who perform the statistical analyses will be blinded to group assignment. Participant’s allocated intervention will be not revealed until the statistical analysis is completed.

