### Interventions

Treatment will be performed by licensed acupuncturists who have at least three years of experience in acupuncture. All the acupuncturists will be trained how to locate acupoints and non-acupoints, puncture, and manipulate needles before the trials. Sterile disposable acupuncture needles (length: 25–40 mm, diameter: 0.25 mm; Hwatuo, Suzhou, China) will be used. Both the acupuncture and sham acupuncture treatments will consist of 12 sessions with 20-min duration over four weeks (three sessions per week, ideally every other day). Acupuncture will be discontinued if the patients suffer from any adverse events (AEs). Other treatments which may affect the dyspepsia symptoms will be prohibited, such as antacids, prokinetics, non-steroidal anti-inflammatory drugs, antidepressant drugs, and so forth.

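### The named primary test for both binary co-primaries of this five-hospital trial, a pooled Fisher's exact test, is valid but conservative and makes no use of hospital

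*Protocol article*

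**What the plan says.** - **Setting** (Protocol article, Study design): "This multi-center, randomized, participant-blind, sham-controlled trial will be conducted at five hospitals in China".
- **Operators** (Interventions; Masking): "Treatment will be performed by licensed acupuncturists who have at least three years of experience in acupuncture", and "masking of acupuncturists is quite difficult to achieve".
- **Allocation** (Randomization and allocation concealment): patients are "randomly assigned to the acupuncture group or sham acupuncture group in a 1:1 ratio with a central web-based randomization", and "The blocked randomization sequence will be computer-generated with the SAS 9.3 software". Hospital strata are neither stated nor excluded. The Discussion adds that the block size is fixed.
- **Test** (Statistical analysis): "Categorical variables will be compared using Fisher’s exact test or Wilcoxon rank-sum test as appropriate". OTE response and elimination of the three symptoms are both yes/no outcomes, so the test that applies is Fisher's. The only other analyses named for the primary outcomes are a subgroup analysis by H. pylori status and a per-protocol sensitivity analysis. No stratified test, hospital term or model appears.
- **Decision rule** (Primary outcomes): both co-primaries must be significant.

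**The concern.** Manual needling by unmasked operators at five hospitals, with outcomes that rest on patients' answers, is a setting where response may well differ by hospital. A pooled 2x2 table turns such differences into noise. If the list is not stratified by hospital, a chance excess of acupuncture patients at a high-response hospital also goes straight into the estimate. If the list is stratified by hospital, the analysis ignores the factor on which patients were randomised, and the pooled test becomes more conservative still.

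Fisher's test also gives away some power with no hospital effect at all. Since both co-primaries must succeed, a loss on each reduces the chance of a positive trial twice over. Hospital is known for every patient, so the loss is avoidable.

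**Working it through.** **Inputs.** From Sample size: OTE 55% v 35%, elimination 26% v 10%, two-sided 0.05, 112 per group, stated powers 82.5% and 84.3%. From Study design: five hospitals. Between-hospital variation is not in the documents; it is assumed and ranged.

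**Step 1: reproduce the plan's powers.** Two-proportion formula with pooled null variance and continuity correction: power = Φ[(d − 1/n − 1.96·SE0)/SE1], where SE0 = √(2p̄(1−p̄)/n) and SE1 = √(p1(1−p1)/n + p2(1−p2)/n).

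- OTE: d = 0.20, p̄ = 0.45, SE0 = 0.0665, SE1 = 0.0651. (0.20 − 0.0089 − 0.1303)/0.0651 = 0.933, so power is 82.5%.
- Elimination: d = 0.16, p̄ = 0.18, SE0 = 0.0513, SE1 = 0.0502. (0.16 − 0.0089 − 0.1006)/0.0502 = 1.005, so power is 84.2%.

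Both agree with the plan. Without the correction the formula gives 85.8% and 88.1%. Exact enumeration of Fisher's test gives 82.8% and 85.6%. The plan was therefore sized for a test of about Fisher's power, with no hospital term.

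**Step 2: the alternative.** With a_k responders among n1k acupuncture patients at hospital k, n0k sham patients, m_k responders in all and N_k patients, the uncorrected CMH statistic is [Σ(a_k − n1k·m_k/N_k)]² / Σ[n1k·n0k·m_k(N_k − m_k)/(N_k²(N_k − 1))], on 1 degree of freedom. The corrected version subtracts 0.5 from the absolute sum.

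**Step 3: power by simulation.** Five equal hospitals, 112 per group, random hospital effects on the log-odds, allocation not stratified by hospital, 20,000 trials per setting. Power in %:

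| SD of hospital log-odds | OTE: Fisher | Pearson | CMH | CMH corrected | Elimination: Fisher | Pearson | CMH | CMH corrected |
|---|---|---|---|---|---|---|---|---|
| 0 | 82.9 | 86.1 | 85.2 | 81.7 | 85.4 | 88.9 | 88.3 | 84.3 |
| 0.25 | 82.7 | 85.9 | 85.5 | 82.3 | 85.4 | 89.1 | 88.6 | 84.7 |
| 0.5 | 82.7 | 86.0 | 86.7 | 83.4 | 84.9 | 88.8 | 88.8 | 84.8 |
| 0.75 | 83.1 | 86.2 | 88.7 | 85.7 | 84.1 | 88.3 | 89.1 | 85.1 |
| 1.0 | 83.1 | 86.1 | 90.8 | 88.0 | 83.9 | 88.1 | 89.8 | 86.0 |

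**Step 4: split the gain.**

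- Fisher to unstratified Pearson is the cost of the exact test: about 3 points for OTE and about 4 for elimination, at every SD.
- Pearson to uncorrected CMH is the part due to hospital. In order of SD it is −0.8, −0.4, +0.7, +2.5 and +4.7 points for OTE, and −0.6, −0.5, 0.0, +0.9 and +1.7 for elimination.

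**Step 5: the same question in terms of hospital rates.** The overall OTE difference is held at 20 points, with 8,000 trials per setting. Fisher stays at about 83%. Uncorrected CMH gives 85–86% with no hospital differences or sham rates of 25–45% across hospitals, and 88–90% at 15–55% to 10–60%. For elimination it is about 83–86% v 87–88%, close to the table.

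**Step 6: size under the null.** With unstratified allocation (Step 3 settings), Fisher rejects in 3.4–4.0% of trials at a 35% rate and 2.6–2.9% at a 10% rate. With allocation balanced within hospital it falls as low as 2.4%. In the Step 5 runs uncorrected CMH held 4.8–5.1%.

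**Step 7: chance imbalance.** If the list is not stratified, hospital mix moves the OTE difference by an SD of about 0.7–2.4 points (hospital SD 0.25–1.0). The standard error is about 6.5 points (SE1 above).

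**The case against.** The case for leaving the plan alone has four parts.

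- **Validity.** Fisher's size stays below 5% in every null setting, under either allocation scheme. A reader might infer bias or an inflated type I error; neither follows. Chance imbalance is random and already within the test's error. This stands: the issue is efficiency and precision.
- **No evidence that hospitals differ.** The article gives no variance and describes common training and standard procedures (Interventions; Quality control). Up to an SD of about 0.5, stratifying by itself gains almost nothing. This stands too, and it is why the hospital part is stated as a range that includes a small loss.
- **Allocation may be stratified.** A reader might infer a single unstratified list from the singular wording of the randomisation section. A condensed article's silence does not show that. If blocks run within hospital, chance imbalance largely disappears, though the pooled test then becomes more conservative.
- **The analysis plan may adjust for centre.** It is not shown, and detail left to it is no fault. But the article does name the test, and a hospital-adjusted primary test elsewhere would have to be reconciled with that sentence.

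A further tempting inference is that hospital differences drag Fisher's power down to about 76% or 69%. Such figures arise if the odds ratio within hospitals is held at 2.27 while sham rates are spread over 15–55% or 10–60%. That shrinks the overall difference to 18.0 or 16.9 points, below the planned 20. With the planned difference held, Fisher stays near 83%. Nor does the article say that outcome assessors differ by hospital.

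**Conclusion.** The point holds as a matter of efficiency. The article commits both co-primaries to a test that is conservative and ignores a factor known for every patient. Replacing it with an uncorrected hospital-stratified CMH test gains about 2 to 8 points of power for OTE, depending on how much hospitals differ, and about 3 to 6 for elimination. Most of the elimination gain, and all of the OTE gain when hospitals are alike, comes from leaving Fisher's test.

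The gains compound under the both-must-succeed rule. By the plan's own product rule, which treats the endpoints as independent, the table gives 82.9% × 85.4% = 70.8% for Fisher v 85.2% × 88.3% = 75.2% for CMH at SD 0. At SD 1.0 it gives 83.1% × 83.9% = 69.7% v 90.8% × 89.8% = 81.5%.

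The figures assume five equal hospitals, a common odds ratio, 112 analysed per group and an assumed hospital variance. With unequal hospitals or a treatment effect that varies by hospital they would change. Recommended, not essential: the planned test would still give a valid answer.

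**What to change.** Before unblinding, replace the test for the two co-primaries with one prespecified method: a hospital-stratified CMH test without continuity correction, or a logistic regression with hospital as a factor. Report the hospital-adjusted risk difference with its 95% CI for each. Also state whether the randomisation list is stratified by hospital; no change to the allocation itself is called for.

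The words on continuity correction matter. With the correction, CMH does no better than Fisher when hospitals differ little (81.7% v 82.9% for OTE at SD 0). The logistic option was not simulated here.

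The cost is about one sentence in the analysis section. Hospital is already recorded and SPSS runs both methods. The statistical price is up to about 1 point of power against an unstratified Pearson test if hospitals turn out not to differ.

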#### Secondary outcomes

OTE at other time points

Response rate according to OTE and the elimination rate of all three cardinal symptoms will also be measured at weeks 8, 12, and 16 after randomization.

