## Severity of dyspepsia symptoms

The severity of eight dyspepsia symptoms, including postprandial fullness, early satiation, upper abdominal bloating, epigastric pain, epigastric burning, nausea, vomit, and belching, will be assessed at baseline, once every week in treatment period and at weeks 8, 12, and 16. The severity of each symptom is scored as asymptomatic (0 point), mild (1 point), moderate (2 points), or severe (3 points) [31].

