### Quality control

The trial protocol is reviewed and revised by the experts in acupuncture, gastroenterology, methodology, and statistics. Prespecified standard operating procedure—including intervention, details in filling eCRF, assessment of outcomes, data management—will be used to train the related staff. An inspection plan will be designed for quality control. Health education and timely follow-up will also be made to improve the compliance of patients. For participants who discontinue acupuncture or deviate from protocol, the outcome assessors will still try to assess the outcomes.

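### The per-protocol rule for the week-4 outcomes counts drug use throughout the trial, so drug use after week 4 can remove patients from a comparison already measured

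*Protocol article*

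**What the plan says.** The Primary outcomes section fixes both co-primaries, OTE response and elimination of the three cardinal symptoms, "at the end of treatment (four weeks after randomization"). The Secondary outcomes section adds that the same two measures "will also be measured at weeks 8, 12, and 16 after randomization".

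Under Statistical analysis, the main analysis is stated first: "All efficacy analyses will be performed using the intent-to-treat (ITT) approach", on all randomised patients, with multiple imputation. Then: "A sensitivity analysis will be conducted for the primary outcome using per-protocol (PP) population". That set requires at least 10 sessions and "no major protocol violations (taking other drugs during the trial, not completing the eCRF as required, etc".) No end date is attached to the drug-use criterion.

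Two other places bear on how far that criterion reaches. The Interventions section says "Other treatments which may affect the dyspepsia symptoms will be prohibited", also without an end date. The section on severity of dyspepsia symptoms schedules assessments "once every week in treatment period and at weeks 8, 12, and 16", so the article has a separate, narrower term for the treatment weeks and does not use it in the PP rule.

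**The concern.** A PP set for a week-4 outcome should depend only on what happened up to week 4. Drug use in weeks 5 to 16 cannot alter an OTE answer or a symptom score recorded at week 4. The reverse influence is plausible: the prohibited treatments are those that may affect dyspepsia symptoms, and patients without relief at week 4 have more reason to take them. A rule that removes patients for later drug use then selects partly on a consequence of the endpoint being analysed.

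This differs from the familiar weakness of PP sets, because it would operate even if nobody broke the protocol during treatment. What is at stake is how the sensitivity analysis can be read. Agreement or disagreement between PP and ITT could reflect behaviour after the endpoint rather than adherence to treatment.

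**Working it through.** **Reach of the rule.** Primary endpoint: week 4. Last assessment: week 16. The rule's wording covers the trial, and the narrower term for the treatment weeks was available. The literal window therefore runs 12 weeks past the endpoint (16 − 4 = 12).

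**Inputs.** The plan gives no figure on this point to reproduce. The Sample size section supplies the expected rates: OTE 55% vs 35%, elimination 26% vs 10% (acupuncture vs sham). The switching rates are assumptions: a share *a* = 5% of week-4 responders and a share *r* of week-4 non-responders take a drug in weeks 5–16. No violations before week 4 are assumed, to isolate the effect of the window.

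**Formula.** PP rate = p(1 − a) / [p(1 − a) + (1 − p)(1 − r)]. Equivalently, the odds of response in an arm are multiplied by (1 − a)/(1 − r). If *a* and *r* are the same in both arms, this factor cancels and the odds ratio does not change.

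**Equal switching, r = 30% in both arms.**
- OTE, acupuncture: 0.5225 / (0.5225 + 0.315) = 62.4%. Sham: 0.3325 / (0.3325 + 0.455) = 42.2%. Difference 20.2 points against a true 20.
- Elimination, acupuncture: 0.247 / (0.247 + 0.518) = 32.3%. Sham: 0.095 / (0.095 + 0.63) = 13.1%. Difference 19.2 points against a true 16.
- Odds ratios stay at 2.27 and 3.16. The elimination difference widens only because both rates rise from a low level.
- In the OTE calculation about 16% of the acupuncture arm and 21% of the sham arm are dropped (1 − 0.8375 and 1 − 0.7875). The OTE and elimination lines are alternative scenarios, since there is only one PP set.

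**Unequal switching among non-responders (acupuncture / sham), OTE.**

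| r | Acupuncture | Sham | Difference | Odds ratio |
|---|---|---|---|---|
| 20% / 40% | 0.5225/0.8825 = 59.2% | 0.3325/0.7225 = 46.0% | 13.2 points | 2.27 × 0.60/0.80 = 1.70 |
| 40% / 20% | 0.5225/0.7925 = 65.9% | 0.3325/0.8525 = 39.0% | 26.9 points | 2.27 × 0.80/0.60 = 3.03 |

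**No true effect, 35% in both arms.** Equal switching gives a difference of 0. The same unequal patterns give 39.0% vs 46.0% (−7 points) or the reverse (+7).

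**Sensitivity to the assumptions.** With no switching among responders and 10% / 30% or 30% / 10% among non-responders, the OTE difference is 14.1 or 26.2 points, and −6 or +6 under no effect. With equal switching of 10% to 40%, OTE runs from 57.6% vs 37.4% to 67.1% vs 47.3%, and the difference stays between 19.8 and 20.2 points.

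**With the window closed at week 4**, later switching removes nobody and the rates stay at 55% vs 35% and 26% vs 10%.

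**The case against.** The strongest reply has four parts.

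*The primary analysis is untouched.* This stands. A reader might infer that drug users leave the main comparison, or that this rule could produce a positive trial. The documents do not support that: the efficacy analyses are ITT on all randomised patients, success requires both primary outcomes to be significant and gives the PP set no role, and outcomes are still sought after deviation ("For participants who discontinue acupuncture or deviate from protocol, the outcome assessors will still try to assess the outcomes").

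*The window is unspecified and belongs in the SAP.* This stands in part. The article never says outright that drug use to week 16 counts, the list of violations is illustrative, and the ban on other treatments sits beside the four-week treatment schedule. But the rule is stated, not omitted, and its plain wording reaches follow-up. If the authors meant the treatment weeks only, the sentence still needs correcting.

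*The sizes rest on invented switching rates.* This stands as a limit on magnitude. The larger distortions need one arm's non-responders to switch at twice the other's rate. Patients are blinded, so under a strict null with intact blinding there is no evident reason for such a gap. If acupuncture does have an effect, a gap needs no unblinding: OTE non-responders range from slightly improved to extremely aggravated, and that mix could differ between arms.

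*The eCRF criterion is a further inference.* This stands. The phrase about the trial's duration attaches to drug use; the eCRF item says only that completion must be as required. Whether a missing week-12 or week-16 page would exclude a patient is unclear, and the link to the week-4 result is weaker for form completion than for drug use.

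**Conclusion.** The point holds for the PP sensitivity analysis and for nothing wider. Followed literally, the rule conditions the analysis of a week-4 outcome on events up to 12 weeks later.

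If non-responders switch more than responders, PP response rates are inflated in both arms, for example OTE 62.4% vs 42.2% instead of 55% vs 35% under 5% and 30% switching. Bias in the odds ratio, and any spurious difference under no effect, requires switching that differs between arms. Under the assumed 20%/40% and 40%/20% patterns, the OTE difference is about 13 or 27 points against a true 20.

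A reader might conclude that the rule favours acupuncture. The documents do not show this: the direction depends on which arm's non-responders switch more, and no switching data are given. That later drug use follows from the week-4 result is plausible, not documented. The change is worth making because the flaw is avoidable and the correction is small.

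**What to change.** In the PP definition under Statistical analysis, replace 'during the trial' with 'before the week-4 assessment'. For the PP analysis of the week-4 outcomes, count only drug use between randomisation and the week-4 assessment, and limit the eCRF criterion to missing data needed for those outcomes. The PP analysis covers the primary outcome only, so no later window is needed. If a SAP already sets a window, align the two texts.

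This changes the analysis-set definition only. It leaves the rule on prohibited treatments, the ITT analysis and the sample size as they are.

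The cost is one clause, recorded as an amendment, and a check of the dates of recorded drug use. No patient is lost from the PP set and some may be kept. The article reports the trial as still recruiting, so the change could be made before unblinding.
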